#### Safety procedures

Published guidance for ensuring participant safety during self-administration of tDCS will be adhered to Knotkova et al. (46). This guidance is as follows: First, training and supervision should be provided to those self-administering tDCS. In TANDEM, all participants will be trained in safe tDCS self-administration, and all treatment sessions will be supervised *via* video-call. Second, the tDCS equipment used must be intended for home use by the lay community. We will use the Newronika HDC stimulator and MindCap electrode placement system which is CE marked for supervised home use in the UK and Europe. This equipment is pre-programmed by the researcher, simple to use, and includes features which prevent misuse (e.g., the researcher can set a minimum time between treatment sessions, and/or set a maximum number of sessions before re-calibration by the researcher). Third, care must be given to the participant's capacity for self-administration. Prior to beginning treatment, the TANDEM researcher will assess each participant's ability to self-administer tDCS safely. Where necessary, additional training will be provided. Participants who cannot safely self-administer tDCS after training will be withdrawn from the study, and the reason for their withdrawal will be reported. Fourth, tDCS tolerance and adverse events must be assessed at each session. Consistently, process outcomes will monitor tDCS tolerance and adverse events at each treatment session (see “Outcome Assessment” for more details), In addition, during or near to the final (T2) assessment, tDCS tolerance and adverse events will be assessed in an optional semi-structured interview about the treatment experience.

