### Outcome assessment

#### Primary outcomes

The primary clinical outcome will be monthly episodes of binge eating, as measured by the Eating Disorders Examination Questionnaire [EDE-Q; i.e., change in the number of monthly episodes of binge eating from baseline (T0) to follow-up (T2)]. Medians and rate ratios (with confidence intervals) will be reported, and these will inform the minimum sample size required for a fully powered large-scale RCT. Rates for recruitment and retention to 8-week follow up will also be reported to provide insight into the time and resources needed for a larger trial.

Intervention acceptability will be assessed in two ways. First, by asking participants the following two questions at post treatment (T1) and follow-up (T2) assessments: (1) “If you could continue with this treatment, would you?” (Yes/No) and “Would you recommend this treatment to a friend who was struggling with binge eating?” (Yes/No). The intervention will be viewed as acceptable if at least 75% of those who receive the real concurrent treatment indicate that they would continue the intervention if given the opportunity and/or if 75% would recommend the treatment to a friend. Second, at or near-to the final (T2) assessment, participants will be invited to complete an optional semi-structured interview about the treatment experience. This will provide qualitative data which will give insight into (a) whether participants viewed the treatment as acceptable and (b) why/why not. Interviews will be recorded, transcribed, and analyzed using thematic analysis.

Feasibility will also be assessed by looking at participant ratings of tDCS tolerability. Participants who receive tDCS will complete a 10-point visual analog scale (VAS) of tDCS discomfort after each session. We will then take the average of ratings across the ten sessions for each participant and use this to assess the average rating for tDCS related discomfort for the real tDCS + ABMT group. The intervention will be considered well-tolerated if this number is ≤4 (i.e., mild discomfort). Prior to beginning each tDCS session, participants will also report any side effects they have experienced since their previous session. The type and frequency of side effects will be reported for consideration.

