### Outcome measures

See Table 1 for a summary of the measures collected at each timepoint.

**Table 1 T1:** Summary of outcome assessment by visit.

	**Screening**	**T0**	**During treatment**	**T1**	**T2**
Eating disorder diagnostic screen	X				
TDCS safety screen	X				
General health and lifestyle questionnaire	X				
Demographics		X			
Eating disorder examination questionnaire (EDE-Q)		X		X	X
Depression, anxiety, stress scale (DASS-21)		X		X	X
Food craving questionnaire—trait version		X		X	X
Clinical impairment assessment (CIA)		X		X	X
Difficulties in emotion regulation scale (DERS)		X		X	X
Barrett impulsiveness scale (BIS-11)		X		X	X
Visual probe task		X		X	X
Food attention network task		X		X	X
N-back task		X		X	
Wisconsin card sorting task		X		X	
Delay discounting task		X		X	
Affective go/no go task		X		X	
VAS measures		X	X	X	X
Assessment of tDCS discomfort/Side effects			X		
Semi-structured interview about treatment (optional)					X

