#### Within session measures

At each treatment session, participants will complete measures of current symptoms and, where relevant, tDCS related discomfort. Before each treatment begins, participants will complete an online “check in” questionnaire which asks about episodes of binge eating since their previous session and, where relevant, adverse events/side effects that may be related to tDCS. They then complete 10-point visual analog scales (VAS) assessing current hunger, feeling of fullness, craving for food, urge to binge, level of tension, level of stress, level of discomfort, and feeling of low mood. At the end of each session, participants complete a “check-out” questionnaire which repeats VAS measures and, where relevant, asks about tDCS related discomfort during the session.

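### The scheduled tDCS side-effect question stops at the last pre-session check-in, so side effects after the last session received are likely to be under-reported

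*Protocol article*

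**What the plan says.** **When side effects are asked.** The Primary outcomes section states: "Prior to beginning each tDCS session, participants will also report any side effects they have experienced since their previous session". The Within session measures section agrees. The online check-in before treatment "asks about episodes of binge eating since their previous session and, where relevant, adverse events/side effects that may be related to tDCS".

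**What is asked after a session.** The check-out form "repeats VAS measures and, where relevant, asks about tDCS related discomfort during the session". Primary outcomes adds: "Participants who receive tDCS will complete a 10-point visual analog scale (VAS) of tDCS discomfort after each session". Neither is a side-effect question.

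**Which visits carry the item.** In Table 1 (Outcome measures) the row "Assessment of tDCS discomfort/Side effects" is marked under the during-treatment column only. T1 and T2 are blank.

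**What comes later.** The Safety procedures section says that "process outcomes will monitor tDCS tolerance and adverse events at each treatment session", and then that "during or near to the final (T2) assessment, tDCS tolerance and adverse events will be assessed in an optional semi-structured interview".

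**Other routes.** The Exclusion criteria section commits to reporting withdrawals, with reasons if participants supply them. Ethical considerations allows withdrawal without a reason.

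**How the data are used.** Primary outcomes promises a report of the kinds of side effect and how often they occurred, with no threshold attached. The tolerability criterion is separate: the mean discomfort rating in the real tDCS arm, averaged over the ten sessions, should be 4 or less.

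**The concern.** A question that looks back from one session to the previous one needs a following session, or a substitute for it, to cover the last interval. The schedule has no substitute. The interval after session 10 has no scheduled question, and neither has the last interval of anyone who stops and does not attend again. The same is true of the 6 weeks from the end of treatment to T2.

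The reports most exposed to this loss are informative ones: a side effect that leads someone to stop, and an effect that appears late or persists. The Introduction says that changes in excitability outlast a session and that repeated sessions may change brain function lastingly, so persisting effects are relevant. The trial is meant to inform a larger study of supervised home tDCS, and side-effect frequencies are among the results that study would use.

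The optional interview is a weak substitute for counting. It is voluntary, takes place about 6 weeks after treatment, and is to be analysed thematically.

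**Working it through.** The article states no side-effect rate or count, so there is no figure to reproduce. The check is a count of covered intervals, followed by an illustration under assumed rates.

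**Inputs from the protocol article**
- 10 sessions over 2–3 weeks (Intervention).
- T2 is 6 weeks after the end of treatment, and study duration is 8 weeks per participant (Trial procedure).
- 22 participants per group recruited (Sample size), so 44 in the two tDCS arms.

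**Input assumed:** a constant probability p of a reportable side effect in each post-session interval, with p from 5% to 40%.

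**Step 1: completers.** The check-in before session 1 has no earlier session to look back to. Check-ins before sessions 2 to 10 cover the intervals after sessions 1 to 9. Coverage is 9 of 10 intervals. The interval after session 10 is open.

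**Step 2: early stoppers.** Someone who stops after session k and attends no further check-in has k−1 of k intervals covered, so the uncovered share is 1/k:

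| k | Covered | Uncovered share |
|---|---|---|
| 1 | 0 of 1 | 100% |
| 2 | 1 of 2 | 50% |
| 5 | 4 of 5 | 20% |

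A person who attends the next check-in, reports the side effect and then declines the session is fully covered up to that point. The 1/k figure does not apply to that person.

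**Step 3: follow-up.** 6 weeks is 42 days; 42/56 = 75% of an 8-week participation has no scheduled side-effect question. No stimulation is given in that time, so this is a share of time and not a share of events.

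**Step 4: illustration, all 22 in the real tDCS arm completing.** Expected reports are 22 × 10 × p. Those falling in the open interval are 22 × p, which is 10% of the total. The share of completers with any side effect is 1 − (1−p)^10 in truth and 1 − (1−p)^9 as captured.

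| p | Expected reports | Missed | Any, true | Any, captured |
|---|---|---|---|---|
| 5% | 11 | 1.1 | 40.1% | 37.0% |
| 10% | 22 | 2.2 | 65.1% | 61.3% |
| 20% | 44 | 4.4 | 89.3% | 86.6% |
| 40% | 88 | 8.8 | 99.4% | 99.0% |

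For completers at a constant rate, the event count is about 10% low and the any-side-effect share falls by 0.4 to 3.8 percentage points. The illustration leaves out early stoppers and delayed effects, for which the article gives no basis for a figure.

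**Step 5: tolerability criterion.** The discomfort rating is taken after each session, including session 10 and the last completed session of a stopper. The side-effect item does not enter it.

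**The case against.** **Other channels exist.** Withdrawal reasons are reported if given, the reason is also reported when someone cannot safely self-administer, every session is supervised by video-call, and T1 and T2 are held by videoconference. This stands in part. It would be wrong to infer that the interview is the only route by which a later side effect could surface. But a volunteered withdrawal reason is not a side-effect question, and the article schedules no such question during the T1 and T2 calls.

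**Stopping does not always mean a missed report.** This stands. A reader might infer that the session before stopping always goes uncaptured. The article does not say how or when people stop, and some may report at a check-in before declining.

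**Tolerability will not look better than it is.** This stands for the stated criterion, which rests on post-session discomfort ratings. A reader might infer that the gap flatters that result; it does not.

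**The full protocol may provide for spontaneous adverse-event reporting and contact after withdrawal.** It may, and it is not shown. Spontaneous reports, however, do not give a frequency with a known number asked. The placement of the scheduled question is stated in the text and in Table 1; it is not a detail that the article leaves out.

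**A T1 question may add little.** This stands. Study design places T1 immediately after treatment, so a form completed straight after session 10 would see little of the following interval.

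**Conclusion.** The point holds as a limited weakness in data collection. As described, the schedule leaves side effects that arise or persist after the last session received to voluntary withdrawal reasons or an optional interview at T2. The reported frequencies are likely to be too low. For completers the loss is small: one interval in ten, and at most about 4 percentage points in the any-side-effect share under the assumed rates. The larger exposure lies with people who stop without returning and with delayed or persisting effects, and the documents do not allow its size to be calculated.

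The direction is a reasoned expectation, not a demonstrated result. It rests on the published schedule being complete for scheduled side-effect questions, and on some side effects occurring in the uncovered periods. The discomfort-based tolerability result is unaffected.

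**What to change.** Give the existing online side-effect check-in, worded to look back to the last session received, to all participants in both tDCS arms at T1 and T2. Offer the same form to anyone who stops early. T2 and the on-stopping form matter most, because T1 may follow session 10 too closely. At T2 the form should be completed before participants are unblinded. Add the marks to Table 1. Report frequencies by arm, with the number of participants asked as denominator at each point.

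Trial progress says that recruitment ended in February 2022 and that data collection was to finish by June 2022. For participants already past these visits, state the gap as a limitation when side effects are reported, and build the question into the planned large-scale trial.

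The cost is a short existing form added to online assessments that are already scheduled: a small extra burden for participants and a minor amendment. Recall over 6 weeks at T2 will be imperfect, which the report should mention.

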#### Concomitant care

As the trial focusses on feasibility rather than efficacy, participants will be allowed to receive other parallel treatments for their ED. Concurrent use of psychoactive medications (excluding neuroleptics or benzodiazepines) will be allowed, providing the dose has been stable for at least 14 days prior to baseline assessment.

### Trial procedure

The individual participant timeline is illustrated in Figure 3. Study duration for each participant is 8 weeks. All participants will partake in assessments at each of the three time points; baseline (T0), post-treatment (T1) and follow-up (T2). Each assessment will be completed *via* videoconferencing (i.e., participants complete both assessments and treatment at home using a laptop or desktop computer with a webcam). Questionnaire measures will be completed online using Qualtrics^XM^ and neurocognitive tasks will be completed online using either Gorilla^TM^ or Millisecond by Inquisit^TM^.

**Figure 3 F3:**
[figure not shown]
TANDEM participant timeline.

Informed consent will be provided *via* an online consent form (Qualtrics^XM^). Once completed, potential participants will be screened over the phone for inclusion in the study. At screening, BED diagnosis is confirmed using a standardized interview [Eating Disorders Diagnostic Screen; (47)]. Physical and psychiatric comorbidities, current medications, and tDCS safety are assessed using a general health questionnaire developed for the purpose of screening. Eligible participants then complete the baseline (T0) assessment. After baseline assessment, participants are randomized to one of four groups: (1) ABMT + real tDCS, (2) ABMT + sham tDCS, (3) ABMT only, or (4) wait-list control group. Intervention groups will then complete 10 sessions of treatment, up to 5 sessions/week, across 2–3 weeks. The waitlist control group will receive no experimental treatment during this time. All participants will complete the post-treatment assessment (T1) after the 10^th^ (final) session of treatment or 2-weeks of waiting, and the follow-up assessment (T2) 6-weeks after completing treatment, or after 8-weeks of waiting. After completing the final (T2) follow-up, waiting control participants will receive ABMT.

### Outcome assessment

#### Primary outcomes

The primary clinical outcome will be monthly episodes of binge eating, as measured by the Eating Disorders Examination Questionnaire [EDE-Q; i.e., change in the number of monthly episodes of binge eating from baseline (T0) to follow-up (T2)]. Medians and rate ratios (with confidence intervals) will be reported, and these will inform the minimum sample size required for a fully powered large-scale RCT. Rates for recruitment and retention to 8-week follow up will also be reported to provide insight into the time and resources needed for a larger trial.

Intervention acceptability will be assessed in two ways. First, by asking participants the following two questions at post treatment (T1) and follow-up (T2) assessments: (1) “If you could continue with this treatment, would you?” (Yes/No) and “Would you recommend this treatment to a friend who was struggling with binge eating?” (Yes/No). The intervention will be viewed as acceptable if at least 75% of those who receive the real concurrent treatment indicate that they would continue the intervention if given the opportunity and/or if 75% would recommend the treatment to a friend. Second, at or near-to the final (T2) assessment, participants will be invited to complete an optional semi-structured interview about the treatment experience. This will provide qualitative data which will give insight into (a) whether participants viewed the treatment as acceptable and (b) why/why not. Interviews will be recorded, transcribed, and analyzed using thematic analysis.

Feasibility will also be assessed by looking at participant ratings of tDCS tolerability. Participants who receive tDCS will complete a 10-point visual analog scale (VAS) of tDCS discomfort after each session. We will then take the average of ratings across the ten sessions for each participant and use this to assess the average rating for tDCS related discomfort for the real tDCS + ABMT group. The intervention will be considered well-tolerated if this number is ≤4 (i.e., mild discomfort). Prior to beginning each tDCS session, participants will also report any side effects they have experienced since their previous session. The type and frequency of side effects will be reported for consideration.

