## Study aims

The primary aim of the TANDEM trial is to assess the feasibility of using 10 sessions of concurrent food-specific ABMT (henceforth, ABMT) and self-administered right-dlPFC anodal tDCS as a treatment for BED. This intervention will be compared to training in combination with sham stimulation, stand-alone training, and a “no treatment” waiting control condition. In doing so, we aim to acquire key information to inform the design of a large-scale RCT.

Specifically, we aim to:
estimate the rate ratio for the proposed primary outcome, change in the number of monthly episodes of binge eating from baseline to follow up. This will inform the sample size calculation for a large-scale RCT.explore the feasibility of conducting a large-scale RCT of at-home self-administered concurrent tDCS and ABMT in adults with BED by assessing recruitment, attendance, and retention rates;assess acceptability by examining participant ratings of treatment acceptability and tolerance, and by evaluating feedback provided during semi-structured interviews;determine the best instruments for measuring primary and secondary outcomes in a full trial by examining the quality, completeness, and variability in the data.

The primary clinical endpoint will be the change in monthly episodes of binge eating from baseline to follow-up. Secondary aims will focus on evaluating changes in overall ED pathology and general psychopathology, changes in attention bias toward high-calorie foods, and changes in executive functioning from baseline to 6-weeks post treatment completion.

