#### Secondary outcomes

Secondary outcomes will be assessed using validated self-report instruments and neuropsychological tasks. Change in score/performance from baseline (T0), to post treatment (T1) and follow up (T2) will be examined by looking at within and between group effect sizes and standard deviations. These data will inform outcome measure selection for a future large-scale RCT.

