### Data analysis

The primary analysis will use the number of episodes of binge eating in a Poisson regression model with baseline adjustment. Descriptive statistics will be used to assess recruitment and retention rates, intervention adherence, and the quality and completeness of the data. In secondary analyses, a mixed model approach will be used to analyse the effect of treatment on primary (PO) and secondary outcomes (SOs), with baseline adjustment. To examine the whether the effect of treatment is different for different levels of overweight or obesity, BMI will be included in the model as an interaction effect. Effect sizes will be analyzed and reported for PO and SOs. For the Poisson regression, rate ratios will be reported. For binary outcomes, odds ratios will be reported. For quantitative outcomes, standardized differences will be reported. Primary parameters will be time vs. treatment interactions at both timepoints after baseline. *P*-values will be reported but for exploratory purposes only (i.e., they will not be interpreted to accept or reject the null hypothesis). The analyses will be done in the intent to treat population, which is defined by including all patients with baseline assessment. Outcome data already obtained for participants who discontinue or deviate from the intervention protocol will be kept and analyzed. Analyses will be conducted using RStudio (62).

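### The inputs named for sizing the full RCT leave out the mean rate and dispersion of the binge count, and an ordinary Poisson confidence interval would not supply the dispersion

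*Protocol article*

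**What the plan says.** The first listed aim, under Study aims, is to estimate the rate ratio for the binge-eating outcome, and of that estimate the article says "This will inform the sample size calculation for a large-scale RCT". Primary outcomes then names the summaries to be used: "Medians and rate ratios (with confidence intervals) will be reported, and these will inform the minimum sample size required" for a fully powered trial. The outcome is a count: "The primary clinical outcome will be monthly episodes of binge eating", taken from the EDE-Q.

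The ratio and its interval come from the model under Data analysis: "The primary analysis will use the number of episodes of binge eating in a Poisson regression model with baseline adjustment". The same section adds "For the Poisson regression, rate ratios will be reported". It mentions no overdispersion term, robust variance or negative binomial alternative.

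Spread is mentioned twice, each time for another purpose. The fourth aim speaks of "examining the quality, completeness, and variability in the data", as the means of choosing instruments for a full trial. Secondary outcomes speaks of "looking at within and between group effect sizes and standard deviations", for secondary measures and to guide outcome selection. No mean, SD or dispersion of the binge count is named as an input to the sample size.

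**The concern.** A Poisson or negative binomial rate ratio compares mean rates. The variance of its logarithm depends on those means and on how much people differ in their underlying rate. A median of a skewed count is not the mean and says nothing about the spread. Anyone sizing the next trial from the named summaries would have to use the median as if it were a mean and would have no figure for dispersion, unless the interval supplied one.

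This is a different matter from the imprecision of a pilot ratio, because the gap would remain even if the rate ratio were known exactly. Informing the size of the next trial is the first listed aim, so the inputs named for it deserve care. If overdispersion is present and does not reach the calculation, the next trial comes out too small.

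**Working it through.** **No figure to reproduce.** The article gives no sample size for the full trial, no episode rate and no dispersion.

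**Inputs.** From Sample size: 80 completers over four arms, so 20 per arm. Assumed: two arms compared 1:1, median 6 episodes a month in the control arm, rate ratio 0.70, two-sided 5%, 90% power, no baseline adjustment. Negative binomial counts have variance m + m²/k, with k = 3, 1 or 0.5, so a smaller k means more spread.

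**Formula.** With control mean m,

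n per arm = (1.960 + 1.282)² × [1/m + 1/(0.7m) + 2/k] / (ln 0.70)²

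Here (1.960 + 1.282)² = 10.51 and (ln 0.70)² = 0.1272, so the multiplier is 82.6. For Poisson counts the 2/k term is dropped.

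**Step 1: median used as a Poisson mean.** 1/6 + 1/4.2 = 0.405, and 82.6 × 0.405 = 33.4 per arm.

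**Step 2: same median, overdispersed counts.** For each k, m is the midpoint of the means that give a median of 6.

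| k | mean m | 1/m + 1/(0.7m) | 2/k | n per arm | ratio to Poisson |
|---|---|---|---|---|---|
| Poisson | 6 | 0.405 | 0 | 33 | 1 |
| 3 | 6.9 | 0.351 | 0.667 | 84 | 2.5 |
| 1 | 8.9 | 0.273 | 2 | 188 | 5.6 |
| 0.5 | 13.5 | 0.180 | 4 | 345 | 10.3 |

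**Step 3: power of a trial sized at 33 per arm when k = 1.** SE of log RR = √(2.273/33) = 0.262. Then 0.357/0.262 = 1.36, and Φ(1.36 − 1.96) gives about 27% power. For k = 3, the SE is √(1.018/33) = 0.176 and power is about 53%.

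**Step 4: does the reported interval close the gap?** With 20 per arm, SE = √(v/20) and the interval is exp(ln 0.70 ± 1.96 SE). The Poisson model-based interval uses v = 1/m + 1/(0.7m). A dispersion-aware interval adds 2/k. The size implied by either interval is 82.6 × v.

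| k | Poisson interval | implied n | dispersion-aware interval | implied n |
|---|---|---|---|---|
| Poisson | 0.53–0.93 | 33 | 0.53–0.93 | 33 |
| 3 | 0.54–0.91 | 29 | 0.45–1.09 | 84 |
| 1 | 0.56–0.88 | 23 | 0.36–1.36 | 188 |
| 0.5 | 0.58–0.84 | 15 | 0.29–1.71 | 345 |

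The dispersion-aware intervals are clearly different, and each leads to its own sample size. The ordinary Poisson intervals hardly differ and move the wrong way. At a fixed median, more dispersion raises the mean, so the interval narrows and the implied trial shrinks while the true requirement grows.

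**Step 5: other assumptions.** With median 12, rate ratio 0.70 and 80% power, the requirement is 13 per arm for Poisson, 73 for k = 2, 132 for k = 1 and 253 for k = 0.5. Over medians 8 to 20 and rate ratios 0.5 to 0.8, the ratio to Poisson is 3.6 to 9.8 for k = 2, 6.1 to 18.6 for k = 1 and 11.4 to 36.3 for k = 0.5.

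**The case against.** The strongest reply is that the quoted sentence includes confidence intervals. A reader might infer that the same reported figures would fit sample sizes differing about tenfold. The documents do not support that, because the interval is one of the reported figures. With arm size known, a dispersion-aware interval determines the variance of the log ratio and so the sample size. This part of the objection stands. What is left is the ordinary Poisson interval, and Poisson regression is the only model named for the primary analysis. The choice of variance estimator may properly sit in an analysis plan that is not shown, so its absence from the article is not the fault raised here.

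A reader might also infer that the next trial will be undersized. The text says these summaries inform the calculation. It does not say that they are the only inputs, that means will go unreported or that the median will serve as a mean. A later statistician would also hold the participant-level counts. That stands too.

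Variability is to be examined for primary as well as secondary outcomes, but its stated use is choosing instruments. Baseline adjustment, which the plan includes, would lower residual dispersion and reduce the gap. Finally, this is a feasibility trial in which p-values "will be reported but for exploratory purposes only". That limits what is at stake within the trial itself, but not for the sample size it is meant to inform.

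**Conclusion.** The point holds in a limited form. The protocol article names inputs for the full trial's sample size that include a summary unable to do the job, the median, and omit two quantities the calculation needs: the mean rate and the dispersion of the binge count. The interval fills the gap in dispersion only if it allows for overdispersion, and the model as named does not ensure that.

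In the main illustration the shortfall runs from 2.5-fold (k = 3) to about tenfold (k = 0.5) relative to Poisson counts. Those multiples rest on an assumed median, rate ratio, power and dispersion, with no baseline adjustment. Pure Poisson is the lower extreme, so tenfold should not be read as a property of this trial. The direction is firmer than the size: if counts are overdispersed and the calculation does not reflect it, the next trial comes out too small. The sentence should be changed, though nothing in the feasibility trial's own conduct is put at risk.

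**What to change.** Amend the sentence under Primary outcomes so that the full trial's sample size is informed by:

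- the mean T2 episode rate and its SD, or negative binomial dispersion, by arm; and
- the rate ratio with a confidence interval that allows for overdispersion (robust, quasi-Poisson or negative binomial).

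Keep medians as descriptive statistics. Retention to follow-up is already to be reported for planning the larger trial and needs no change.

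The cost is one reworded sentence and one extra table, from EDE-Q data already scheduled at T0, T1 and T2. The downside is that the projected size of the next trial may look larger.
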